#### Inclusion criteria

Patients will be eligible for each phase of the study if they are (1) ≥ 18 years of age, (2) HIV-infected as confirmed by medical record review, (3) prescribed an ART regimen, and (4) meet DSM-V criteria for a substance use disorder (other than tobacco, marijuana, and alcohol) over the past 90 days. Although heavy alcohol consumption affects ART adherence and cannabis use has demonstrated mixed results in the literature, we chose to narrow the target population to illicit drug use to have a more homogenous sample for this pilot trial. In Phase 3 (pilot randomized trial), participants must also report < 100% adherence to ART regimen and have experienced a detectable viral load (> 20 copies/mL) within the last 6 months. Our eligibility criteria for a substance use disorder is broad given the LS-DU will focus on improving ART adherence and linking patients to appropriate substance use treatment resources. Our goal is to create an intervention that is easily implemented in clinical settings. We will examine qualitative data from Phase 1 to assess the potential need for the intervention to take a more narrow approach and adjust the manual development based on these data.

Clinicians were eligible to participate in Phase 1 provider interviews if they were: over the age of 18, employed at a local HIV clinic or substance use treatment facility, and had > 6 months experience working with patients living with HIV and/or patients with a substance use disorder.

#### Exclusion criteria

Exclusion criteria for all study phases include issues that jeopardize informed consent, including cognitive impairments, active psychosis, current suicidal ideation, and not being fluent in English. Patient participants will be administered a brief measure of capacity to consent [15].

### Study enrollment and randomization

In accordance with institutional review board procedures, participants will be recruited from an academic affiliated HIV treatment center which is funded by the Ryan White program and situated in an urban region. We will hang flyers for each phase of the study to advertise study details. A research assistant will pre-screen medical records of patients with clinic appointments and identify those who appear to be eligible. Written informed consent will be obtained from those interested in participating.

### Phase 1 procedures: qualitative methods to inform intervention adaptation

#### Overview

Individual interviews have been conducted with 29 treatment providers (n = 16 HIV providers; n = 13 substance use providers) and six PLWH who met eligibility criteria to gather feedback on the Life Steps protocol, ideas for adapting the protocol to PWUD, and training preferences. Interview topics included: (1) current support for HIV care within the clinic or community for HPWUD, (2) brainstorming intervention content, (3) critique of proposed intervention content and existing materials, and (4) evaluation of intervention length, intensity, frequency, and mode of delivery. Patient and provider data are being analyzed and triangulated to inform adaptation of the Life Steps intervention to HIV-infected PWUD. Patients and providers received $40 for participating in a 60–90 min qualitative interview.

#### Manual development

The Life Steps manual will be enhanced to address the most salient needs of HIV-infected PWUD while retaining the core elements of the intervention. Data from Phase 1 will guide modification of the manual. The manual will be evaluated based on the theoretical model, targeted outcomes, therapeutic strategies, and content. *Substantive Changes Expected*. Based on extant literature, there are two key areas in which substantive changes are expected in the adaptation of the Life Steps manual (see Table 2): *Content*. The Information-Motivation Behavioral Model [16] will guide content targeting individual knowledge, motivation, and skills development (see Fig. 1). Considering the synergistic interaction of HIV and drug use on nonadherence, syndemics theory [1] will guide the adaptation of intervention content to address contextual challenges of HIV-infected PWUD (e.g., stigma, stress, poverty). *Delivery*. Based on the hypothesized outcomes from Phase 1, we expect the adapted LS-DU protocol will contain a new drug use module focused on building motivation for change and linkage to substance use treatment; this module will be informed by best practices in the BMI literature. While we have anticipated preliminary adaptations based on the extant literature, changes to the protocol will be based on data obtained during the qualitative phase which will be sufficiently broad and open to assess for factors that we have not anticipated. Once the manual is developed, a review panel of five experts in HIV, addiction, and ART adherence will provide feedback about the intervention manual. We will use an affinity grouping procedure to merge similar recommendations. The draft of recommendations will be reviewed through two rounds of preliminary ratings, teleconference discussions, and written comments to result in a set of final recommendations which will inform revision and finalization of the manual.

**Table 2 Tab2:** Core elements of life steps and anticipated modifications

Module	Description	Anticipated modifications to life steps
*Existing life steps protocol*		
Step 1: Education and introduction	Information about how medication adherence plays in successful treatment is provided. The aim is to increase knowledge and self-efficacy to influence treatment success and introduce problem-solving for medication adherence	Information regarding the physiological and psychosocial impact drug use has in PLWH, address impact on ART medications and increased HIV transmission
Step 2: Transportation to appointments	Problem-solving strategies, brief cognitive restructuring, and rehearsal techniques are provided to address transportation issues to prevent missed appointments with health care providers	No anticipated modifications
Step 3: Obtaining medications	Develop a plan for continues access to medications. Address concerns about patient’s privacy and confidentiality during interactions with the pharmacist	No anticipated modifications
Step 4: Communicating with health care providers	Brief cognitive techniques are suggested for irrational fears about asking questions	Address concerns about drug use stigma; teach strategies for improving patient-provider relationship
Step 5: Coping with side effects	Learn to (a) pick a regimen with their doctor to minimize side effects; (b) re-interpret side effects as signs that medications are in their bloodstream and working; and (c) increase the salience of benefits of adherence	No anticipated modifications
Step 6: Formulating daily medication schedule	Patients complete a detailed map of an average day of pill-taking, specifying environmental and other cues for pill-taking throughout the day	Address challenges to maintaining the daily medication schedule during periods of intoxication
Step 7: Storing medications	Problem-solving techniques for storing medications when not at home	No anticipated modifications
Step 8: Cues for pill-taking	Taught how to use cues to remember to take pills (e.g., setting alarms, reminder system). Adaptive cognitions for adherence are rehearsed	No anticipated modifications
Step 9: Response to slips in adherence	Patients are taught how to handle slips and to avoid all-or-nothing thoughts. Cognitive techniques to cope with a lapse are discussed	Address how drug use may result in slips on adherence and how to minimize negative health outcomes
Step 10: Review	Review previous steps and address concerns	No anticipated modifications
*Anticipated additional adherence*-*related modules to the life steps protocol (based on the syndemics model by Singer* [1]*)*		
Interpersonal factors		
Increasing social support and relationship stability	Brief training in interpersonal skills and strategies to help increase support networks and build healthy relationships	
Individual factors		
Psychiatric comorbidities	Participants will receive a list of local mental health and substance abuse treatment options	
HIV-related beliefs	Address interaction toxicity beliefs in regards to taking ARTs while using drugs and alcohol	
Environmental factors		
Stigma	Cognitive techniques will be provided to help participants cope with stigma related to HIV and drug use	
Access to services	Participants will receive a list of local resources to assist with housing, transportation, and food insecurity	
*Anticipated additional drug use modules to the life steps protocol (based on the FRAMES approach by **Miller and Sanchez *[23]*)*		
Personalized assessment and feedback	Participants will complete a baseline assessment of their drug use ad risk behaviors. Individualized feedback regarding personal risk or impairment will be given following assessment	
Changing risk behaviors	Use of MI techniques to address drug use and other risk behaviors. Techniques include assessing stage of change, use of decisional balance, address discrepancies between personal goals and behavior, and emphasize that autonomy and responsibility for change is explicitly on the participant	
Advice about changing	Advice about reducing or stopping drug use will be given to the participant in a nonjudgmental manner	
Treatment options	A menu of self-directed change options and treatment alternatives will be offered to the participant	
Empathic counseling	The clinician will show warmth, respect, and understanding towards the participant	
Self-efficacy for change	Self-efficacy to change drug use will be engendered in the participant to encourage change

**Fig. 1 Fig1:**
[figure not shown]
Information–motivation–behavioral skills model of ART adherence (Adapted from Fisher et al. [16])

### Phase 2 procedures: piloting and training of community-based facilitators

#### Therapist training, fidelity, and competence

Following manual refinement, two master’s-level community clinicians will be trained in fidelity and competence with the intervention protocol. Training will consist of a half-day didactic workshop, followed by video-taped role plays, which will be coded by two independent raters for fidelity and competence. We will assess competence using the Motivational Interviewing Treatment Integrity 2.0 (MITI) [17] and the Yale Adherence and Competency Scale [18]. Following training, clinicians will provide feedback regarding their training experience and recommendations for the training protocol.

#### Patient qualitative interviews

The two trained clinicians will deliver the LS-DU intervention to 8–12 HIV-infected PWUD using an iterative process. We will conduct exit interviews with patients and the two clinicians following completion of the intervention to assess intervention acceptability and feasibility. Data collected during the individual interviews will include: (1) critique of intervention content and materials, (2) evaluation of intervention length, intensity, frequency, and mode of delivery, and (3) suggestions to further enhance the intervention. Patients will again receive $40 for participating in a 60-min qualitative interview. Interviews will be administered until saturation is reached.

### Phase 3 procedures: type 1 hybrid effectiveness-implementation pilot trial

#### Overview

Following the open trial, a pilot type 1 hybrid randomized effectiveness-implementation trial will be conducted to determine the effectiveness of the LS-DU protocol relative to health education. Hybrid effectiveness-implementation trials are designs that simultaneously gather data on treatment effectiveness and implementation outcomes [19]. In a type 1 hybrid trial, the primary emphasis is on the evaluation of treatment effectiveness, and the secondary emphasis is on the collection of data on implementation outcomes. Because the current study is designed to collect pilot data for a future study, measures of acceptability and feasibility are defined as the primary outcomes. Measures of effectiveness are then defined as the secondary outcomes, while data on implementation effectiveness are gathered as an exploratory outcome.

All participants will complete a baseline assessment consisting of a series of self-report measures and a urine toxicology screen. Following completion of the baseline assessment, participants will begin 2 weeks of baseline ART adherence data collection using an electronic pill cap monitoring system (MEMScaps). Only after completing the MEMS data collection will patients be randomly assigned to treatment condition using urn randomization [20] controlling for gender and viral load.

#### Treatment conditions

Participants will be randomized to either the LS-DU experimental intervention or the health education control. We considered using the original Life Steps as a comparator condition; however, we believe that a minimally active, but ethical control group is the most direct test of the intervention (relative to treatment as usual). A more active control intervention, such as the original Life Steps protocol, may attenuate potential effects and would require a much larger sample size. The LS-DU intervention will utilize the manual refined at the end of Phase 2. Health education is a time-matched control condition that covers a variety of general health topics and has proven to be a credible control condition in prior studies [21]. Intervention clinicians will be given a health education training manual and will complete videotaped role plays. Two independent coders will assess fidelity to the health education intervention using a topic checklist. Both conditions will consist of two in-person intervention sessions of 60 min duration separated by 1 week. The LS-DU intervention will also consist of two follow-up booster phone sessions at 1 and 2 months following the last in-person session.

#### Assessments

With the exception of demographic data, all of the measures described below will be administered at baseline and the three follow-up assessments. To enhance retention, participants will receive an escalating compensation schedule in gift cards for completion of the 1-, 3-, and 6-month follow-ups. Participants will receive a breathalyzer test prior to each assessment, and impaired participants will be rescheduled.

The Information-Motivation Behavioral Model [16] has informed the battery of measures. The following basic demographic data will be collected: age, gender, race, ethnicity, current living situation, marital status, sexual orientation, educational attainment, employment status, date of HIV diagnosis and ART initiation, mode of transmission, substance use diagnosis, and the intensity and duration of the substance use disorder. Primary outcomes will be feasibility and acceptability of the LS-DU and assessment procedures to be used in a larger trial. We will assess preliminary effectiveness of the LS-DU in a real-world clinical setting delivered by trained community-based clinicians. Effectiveness outcomes will include ART adherence measured by MEMScaps, viral load, and substance use measured by the 30-day Timeline Followback. Implementation outcomes will include readiness to adopt and qualitative data on barriers and facilitators to uptake. We will also gather exploratory data on the following potential moderators of the LS-DU intervention: HIV treatment self-efficacy, depression, HIV treatment retention, and HIV and substance use problem behaviors measured by the Addiction Severity Index (see Table 3 for measures).

**Table 3 Tab3:** Outcome variables and assessment points

Quantitative measures	Stakeholder	BL	1-, 3-mos follow-up	6-mos follow-up
Demographics	All	X		
*Acceptability*				
Program satisfaction questionnaire	Patients, clinicians			X
*Effectiveness*				
Medication adherence (MEMS)	Patients	X	X	X
Viral load	Patients	X		X
Substance use	Patients	X	X	X
*Implementation*				
Organizational readiness for change assessment tool	Clinic directors	X		
*Exploratory*				
HIV treatment self-efficacy	Patients	X	X	X
Depression	Patients	X	X	X
HIV treatment retention	Patients	X	X	X
Substance use risk behaviors	Patients	X	X	X

We will evaluate the implementation context and sustainability potential of the LS-DU at the clinic level through surveys and semi-structured interviews. Individual interviews will be conducted post-intervention with clinicians and clinic leadership. Data will be collected regarding perceptions of providers and leadership concerning barriers/facilitators to intervention adoption, tools needed to deliver the intervention consistently, resources needed to maintain the intervention long-term, and adaptations needed to integrate into regular practice. Providers and leadership will complete the Organizational Readiness for Implementing Change Scale [22] to examine organizational strengths/weaknesses that support sustainability of the intervention.

#### Quantitative data analysis plan

Considering this is a pilot project, analyses will have the goal of establishing feasibility and estimation of effect sizes, with modest expectations for rejection of the null hypotheses. As a first step, the equivalence of treatment condition assignment with regard to key baseline variables will be assessed on demographic characteristics, baseline ART adherence measures (self-report and viral load), drug category and addiction severity, and baseline levels of potential treatment mechanisms and moderators using tests of proportions or t-tests as appropriate. Should conditions differ on any characteristic; these variables will be used as covariates in outcome analyses. Other preliminary analyses will include patterns of missing data, research dropout rates, distributional properties of dependent and other measures, and correlations among outcome measures.

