##### Effectiveness

We will measure treatment effectiveness via adherence to HIV medication (MEMScaps), viral load (eligibility screener vs. baseline vs. 6-months), and days of drug use (Timeline Followback). Separate Generalized Estimating Equation (GEE) models for adherence will be generated for proportion of days on which study medication was taken (as indicated by MEMScap) and the proportion of expected pills taken at the 1-, 3-, and 6-month follow-ups. Examining interactions between intervention and time will test differences in adherence over the course of the intervention across the intervention conditions. As our sample size limits our ability to conduct sophisticated longitudinal analyses, we will use GEE with caution and will revert to more standard general linear models should we encounter model convergence problems. Additional measures of treatment effectiveness, including self-reported adherence, viral load, and drug use, will also be analyzed using GEE.

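### Covariates for the effectiveness models are chosen by baseline tests between randomised arms, while baseline pill-cap adherence and the urn factors are not prespecified as model terms

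*Protocol article*

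**What the plan says.** All references are to the protocol article.

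- **Quantitative data analysis plan.** Baseline equivalence of the arms is assessed "using tests of proportions or t-tests as appropriate". The variables are demographics, adherence, drug category, addiction severity, and possible mechanisms and moderators. The consequence is fixed: "Should conditions differ on any characteristic; these variables will be used as covariates in outcome analyses". The adherence measures named for the check are "baseline ART adherence measures (self-report and viral load"). No significance threshold is given.
- **Phase 3, Overview.** Before assignment, "participants will begin 2 weeks of baseline ART adherence data collection using an electronic pill cap monitoring system (MEMScaps"). Assignment is then made "using urn randomization [20] controlling for gender and viral load".
- **Effectiveness.** Separate GEE models take the proportion of days with medication taken and "the proportion of expected pills taken at the 1-, 3-, and 6-month follow-ups". Differences between conditions are examined through intervention-by-time interactions. No baseline adherence term and no urn factor is named. For viral load only, the baseline value is listed among the comparison points.
- **Table 3.** MEMS adherence, viral load and substance use are all scheduled at baseline.

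**The concern.** In a randomised comparison the null hypothesis of a baseline test is true by design, so a significant result reflects chance. A non-significant one, with 30 per arm, is weak evidence of similarity. A rule that turns such tests into a covariate list has two effects. It can bring in variables that do not predict the outcome, and it leaves out strong predictors that happen to be balanced. The analysis model is then unknown until the baseline data have been tested.

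The likeliest strong predictor of follow-up MEMS adherence is baseline MEMS adherence. It is available for every randomised participant by design, yet the screen names other adherence measures and the model names follow-up values only. Gender and viral load are in the tested set, but the urn scheme works against their differing, so the rule is unlikely to bring in the factors used in the allocation.

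At stake is the precision of the effectiveness estimates. The Participants section and the analysis plan both make effect-size estimation a goal of this trial, so precision matters even in a pilot.

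**Working it through.** **Inputs.** From the documents: 30 per arm, d = .40 to .60, stated power .54 to .75, and .80 at d = .65 (Participants). Assumed, because not stated: α = .05, and a baseline-to-follow-up correlation r of .3, .5 or .7.

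**1. The plan's own power figures.** These come from a two-sample t-test with 58 df and noncentrality d·√(30/2).

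| d | two-sided .05 | one-sided .05 | stated |
|---|---|---|---|
| .40 | .33 | .455 | .54 |
| .60 | .63 | .743 | .75 |
| .65 | .70 | .800 | .80 |

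The stated .75 and .80 agree with a one-sided test; .54 agrees with neither. That is a separate matter. The two-sided column is the reference below.

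**2. Chance differences at baseline.** For k independent tests, P(at least one) = 1 − .95^k.

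- k = 10: .401
- k = 20: .642, with 20 × .05 = 1 variable selected on average

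The variables listed under Assessments and in the analysis plan come to roughly 20. The plan speaks only of key variables, hence the range from 10. Correlation among the measures would change these figures.

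**3. Always adjusting for baseline, linear comparison at one visit.** The variance factor is 1 − r², the equivalent N is 60/(1 − r²), and the noncentrality at d = .60 is .60·√15/√(1 − r²) = 2.324/√(1 − r²).

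| r | variance factor | reduction | equivalent N | noncentrality | two-sided power |
|---|---|---|---|---|---|
| none | 1.00 | – | 60 | 2.324 | .63 |
| .3 | .91 | 9% | 66 | 2.436 | .67 |
| .5 | .75 | 25% | 80 | 2.683 | .75 |
| .7 | .51 | 49% | 118 | 3.254 | .89 |

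**4. The stated rule against fixed adjustment.** This is a simulation of 40,000 trials with 30 per arm and one prognostic baseline variable that is in the screen.

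| r | power at d = .60, test-then-adjust | power at d = .60, always adjust | type I error, test-then-adjust |
|---|---|---|---|
| .3 | .63 | .66 | .049 |
| .5 | .64 | .75 | .041 |
| .7 | .65 | .89 | .037 |

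The rule selected the variable in about 5% of trials. At r = .5 the variance of the estimate was .066 unadjusted, .062 under the rule and .051 with fixed adjustment. Baseline MEMS is not even named in the screen, so for that variable the rule offers no stated route in.

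**5. Which contrast benefits.** Suppose only follow-up values are modelled and the baseline value enters as a main effect β·X. The difference between two visits in one participant then contains βX − βX = 0. A treatment-by-time contrast among follow-up visits therefore gains about nothing when β is similar across visits. The gain in step 3 belongs to the between-arm effect at a visit or averaged over visits. If baseline is instead an unconstrained time point, a change-from-baseline contrast has relative variance 2(1 − r): 1.40, 1.00 and .60 at r = .3, .5 and .7, against .91, .75 and .51 with baseline as a covariate.

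**The case against.** **The article is condensed.** A full covariate list is commonly left to an analysis plan, and nothing in the Effectiveness section excludes baseline MEMS, gender or viral load. This stands in part: a reader might infer that the plan forbids these terms, and it does not. But the selection rule is stated, not omitted, and a fuller document that followed it would carry the fault forward.

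**Baseline may already be used as a time point.** Table 3 schedules MEMS at baseline, and for viral load the baseline value is a named comparison point. For adherence the Effectiveness section names follow-ups only, so this is unsettled. Even then, step 5 shows that a change contrast is less precise than covariate adjustment.

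**The power gain is for another analysis.** This stands. A reader might take the table in step 3 as the gain for the planned GEE test. It is not: the planned test is an intervention-by-time interaction, and the Participants section reports adherence effects as odds ratios. The 1 − r² rule does not carry over to odds ratios, where adjustment also moves the target from a marginal to a conditional effect.

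**The inputs are assumed.** This stands. No correlation, threshold or test count is given, and at r = .3 the gain is small. A two-week baseline and entry restricted to imperfect adherence could both lower r.

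**It is a pilot.** The primary outcomes are acceptability and feasibility, which the rule does not touch. This limits the severity, but effect-size estimation remains a declared goal.

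**Conclusion.** The point holds as a fault in a stated method. The adjustment set is decided by chance imbalance, the tests cannot show equivalence, and baseline MEMS and the urn factors have no assured place in the models. If r is .3 to .7, fixed adjustment would reduce the variance of a linear between-arm comparison by about 9% to 49%, whereas the stated rule recovers little of that gain. The 40% to 64% chance of at least one spurious difference rests on 10 to 20 independent tests at .05.

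A reader might infer that the rule inflates false positives or invalidates the trial's conclusions. The evidence points the other way: simulated type I error was .037 to .049, slightly conservative, and no primary outcome is affected. The consequence is imprecision and an unpredictable model for secondary estimates. This should be fixed, but it is not critical.

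**What to change.** 1. Delete the test-then-adjust rule. Describe the arms at baseline without using p-values to select covariates.
2. In every effectiveness model, prespecify the baseline value of that outcome: the two-week MEMS proportion for adherence, baseline viral load for viral load, and baseline Timeline Followback days for drug use. Add gender and viral load as the urn factors, with viral load entered once in the viral-load model.
3. Name the between-arm effect at a stated follow-up visit, or averaged over the follow-up visits, as the effect to be estimated, since that is where baseline adjustment helps. Where odds ratios are reported, say whether they are marginal or conditional.

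The cost is wording and two to three degrees of freedom per model. All the variables are already collected. The change should be made before outcome data are examined by arm.
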